#### Recruitment procedures

Within each study clinic, the research staff will identify HIV-positive participants who have been on ART and provide them with a brief overview of the study. Interested individuals will then be referred to a fieldworker, who will request informed consent for the completion of a brief screener for assessing whether or not they meet the eligibility criteria listed above. With one of the proposed inclusion criteria being classified as a “harmful/hazardous drinker” (have six (or four, if female) or more drinks on one occasion at least weekly, and score no more than 22 on the AUDIT), those with AUDIT scores in the range of possibly dependent (>22) will not be eligible for the study, hence they will not get to the randomisation stage. Once the participant has consented to take part in the study he/she will be assigned a random ID number which will determine the condition into which he/she will be placed: the alcohol-reduction intervention condition, the wellness intervention condition, or the TAU condition. Consenting individuals will then be asked to provide a sample of just under 25 ml of venous blood, to assess biomarkers that are indicative of recent levels of alcohol consumption and assess their HIV viral load and CD4 T-cell counts. The blood samples will be drawn by a registered nurse or phlebotomist in a private space and transported to a local laboratory for testing. The participants will then be interviewed by a fieldworker on their demographic characteristics, alcohol-related issues, ART adherence, and health-related issues. The interviews will be conducted by a trained interviewer who will be independent of the interventionists and clinic staff. Participants assigned to the alcohol reduction and wellness conditions will then be asked to return within one week (or two weeks, if not available during the following week) to receive their first and second intervention sessions, and return after another week, to receive their third and fourth intervention sessions. All participants, irrespective of condition assignment will be asked to return at three, six and twelve months’ post-randomisation to complete follow-up assessments (interviews and further biological testing). Participants’ transport costs will be covered for each contact with project staff.

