#### Randomisation and blinding

Randomisation to one of the three conditions will occur at each of the four sites, i.e. the randomisation will be stratified by site. The randomisation code will be generated by computer generated tables. Treatment allocation will be done by site supervisors using pre-prepared consecutively numbered sealed, opaque envelopes, which will contain the group assignment. Fieldworkers will conduct the post-intervention outcome assessments masked to treatment allocation to ensure that the assessments remain unbiased and independent from the intervention sessions. Each counsellor will take part in only one intervention arm, and the wellness and alcohol reduction interventions will be run on different days of the week (based on alternating biweekly schedule) to minimise contact between participants who are randomly allocated to different arms, and to minimise contamination across the study arms. Given the study’s behavioural nature, the interventionists will not be blinded to which intervention the participants receive.

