##### Condition 3: Treatment as usual (TAU)

Participants in this condition will receive the standard package of care for PLWHA and on ART who also drink at hazardous/harmful levels. Typically, if a health care provider suspects adherence problems (by self-report or clinical indicators), the patient is referred to adherence counsellors for additional counselling. There are no firm guidelines on the duration or content of this counselling. Counsellors are left to determine how best to address adherence problems with the patient. If adherence counsellors or primary health care providers suspect alcohol problems, they usually refer patients to on-site clinical psychologists/clinical social workers, if available, or off-site community mental health (CMH) or alcohol services. We will monitor the number of visits the TAU patients make for adherence and alcohol support, and type(s) of support services received (e.g. advice, referral) by means of self-report at the 3, 6, and 12 month follow-ups.

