Ethical approval for this study has been obtained from the Medical Research Council’s Ethics Committee. Approval to conduct the study has also been obtained from the Regional and Provincial Departments of Health, and the site managers of each clinic. Participants will be informed that their decision to participate in the study is voluntary and will not affect their current or future care at the clinic. They will also be informed that even after deciding to participate in the study, they can still decline to answer questions or to take part in specific activities, and they may terminate their participation at any time without any penalty. Informed consent will be obtained by research staff who are not clinic employees or connected to participants’ medical care. Through the informed consent process, prospective participants will be informed of all foreseeable risks involved in the study. Individuals with low or no literacy will have the consent form read to them by a person of their choosing, and verbal consent will be obtained, witnessed by an independent person. The consent forms will be translated and back-translated and adapted for cultural appropriateness and readability into SeTswana and seSotho, the main local languages of the region. To ensure confidentiality, study data and biological samples will be identifiable only by randomly generated participant identification numbers and will not contain participants’ names or any other personal identifying information or protected health information. All electronic data sources will be encrypted and password protected. Research personnel who have contact with participants will be asked to sign a confidentiality agreement, and receive on-going training and supervision on ethical conduct and confidentiality protection. To minimise the possibility of a breach of confidentiality by participants during the focus group discussions, the participants will be asked to not disclose the identity or the content of the commentary of any of their fellow focus group discussion members to anyone outside of the focus group.

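### The arm is fixed by an ID number before baseline data are collected, and this is not reconciled with the sealed-envelope allocation

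*Protocol article*

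**What the plan says.** The Recruitment procedures section gives a sequence. After screening and consent, the participant is "assigned a random ID number which will determine the condition into which he/she will be placed". The text continues: "Consenting individuals will then be asked to provide a sample of just under 25 ml of venous blood". Then: "The participants will then be interviewed by a fieldworker on their demographic characteristics, alcohol-related issues, ART adherence, and health-related issues". Only after that comes the scheduling of sessions: "Participants assigned to the alcohol reduction and wellness conditions will then be asked to return within one week".

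The Randomisation and blinding section describes a computer-generated code, stratified by site, and a different act of allocation: "Treatment allocation will be done by site supervisors using pre-prepared consecutively numbered sealed, opaque envelopes". The envelope holds the assignment. On masking it says: "Fieldworkers will conduct the post-intervention outcome assessments masked to treatment allocation". It makes no such statement for the baseline interview, whose interviewer is described in Recruitment procedures as independent of interventionists and clinic staff, but not as masked.

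The Ethics section says that "study data and biological samples will be identifiable only by randomly generated participant identification numbers". The description of the treatment-as-usual (TAU) condition adds a follow-up item, collected by self-report at 3, 6 and 12 months: "We will monitor the number of visits the TAU patients make for adherence and alcohol support".

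**The concern.** Baseline data are safest when they are complete before anyone can know the arm. Here the stated order puts the arm-determining step first. The main outcome is self-reported drinking, and its baseline value is used for adjustment. A participant or interviewer who knew the arm could shade the baseline report differently by arm, and adjustment would carry that difference into the treatment effect.

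Two further matters follow from the same text. Someone who leaves between ID assignment and interview is already randomised but has no baseline, which is awkward for an intention-to-treat analysis that includes everyone as allocated. And if the number that determines the arm is also the number on forms and tubes, concealment and masking depend on nobody at the site being able to link the number to the arm. The protocol gives no assurance on that.

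**Working it through.** The protocol gives no figure on this point to reproduce, so the first check sets the sections side by side.

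1. **Order.** Recruitment procedures: eligibility, consent, ID that determines the arm, blood, interview, invitation to sessions. The Design section calls the first observation pre-intervention; nowhere is it called pre-randomisation. As written, assignment precedes all baseline measurement other than screening.
2. **Mechanism.** Under Recruitment procedures the arm follows from a random ID number. Under Randomisation and blinding it follows from the next consecutively numbered envelope, that is, from order of enrolment within site. The two agree only if the ID number does no more than point to an envelope. The protocol does not say so, and a random number fits consecutive numbering poorly.
3. **Timing of disclosure.** Neither section says when the envelope is opened relative to the baseline interview. The first step that requires anyone to know the arm is the invitation to sessions, which is described after the interview.
4. **Masking.** It is stated for follow-up and not for baseline.
5. **Reach of the ID.** The Ethics section labels data and samples with randomly generated participant numbers. This appears to be the same number as in Recruitment procedures, though the protocol does not say so outright.
6. **Role of baseline.** The analysis section for phase 2 names analysis of covariance using pre- and post-treatment means, alongside repeated-measures analysis of variance and two-sample tests.

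The second check shows how a baseline error would pass through the analysis of covariance. It is illustrative only.

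- Input from the sample size section: correlation 0.7 between measurements, one baseline and three follow-up measures. Equal SDs over time are assumed.
- Slope of the follow-up mean on baseline: cov/var = 0.7.
- Adjusted difference = (difference in follow-up means) − 0.7 × (difference in baseline means). A spurious baseline difference of b SD therefore shifts it by 0.7b SD in size.
- The protocol gives no value for b. Assumed range: b = 0.1 gives 0.07 SD; b = 0.2 gives 0.14 SD; b = 0.3 gives 0.21 SD.

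Two yardsticks for those values:

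- *Detectable difference at the final sample.* 600 less 20% attrition is 480 completers: 240 alcohol, 120 wellness, 120 TAU. Variance factor: (1 + 2 × 0.7)/3 − 0.7² = 0.80 − 0.49 = 0.31. With two-sided 5% and 90% power (1.960 + 1.2815 = 3.2415), for alcohol against one comparator: 3.2415 × √(0.31 × (1/240 + 1/120)) = 3.2415 × √0.003875 = 0.20 SD.
- *Planning effect.* (4.75 − 3.58)/√((1.81² + 3.22²)/2) = 1.17/2.61 = 0.45 SD.

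The assumed range of 0.07 to 0.21 SD runs from about a third of the detectable difference to all of it (0.07/0.20 = 0.35; 0.21/0.20 = 1.05), and from about a sixth to just under half of the planning effect (0.07/0.45 = 0.16; 0.21/0.45 = 0.47).

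**The case against.** The strongest reply is that assignment is not disclosure. A reader might infer that the baseline interview is conducted with the arm known. The text does not say so: sessions are arranged after the interview, site supervisors rather than interviewers allocate, and the interviewer is independent of those delivering the interventions. This stands, so the point is an unprotected step and not a stated breach.

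A reader might also infer that the two sections flatly contradict each other. They need not: the ID could simply index an envelope. What remains is that the link is unexplained, so sites could follow either procedure and claim compliance.

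Nor does the text support a claim that the ID reveals the arm to follow-up staff. It is described as random, no section gives fieldworkers a key, and masking at follow-up is expressly promised.

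It is tempting to read the TAU item as asked of TAU patients alone, which would identify the arm to a masked fieldworker and leave outside support unmeasured elsewhere. The sentence sits within the description of that condition and does not say that the other arms are not asked. That reading is not established; a clarification is enough.

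Finally, the values of b have no source in the protocol and presuppose knowledge of the arm. Two-sample tests, also listed, would not carry the error if applied to follow-up values alone. Loss between assignment and interview may be small, since the steps follow one another with no stated interval. These limits stand. None of them changes the stated order or supplies the missing link between ID and envelope.

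**Conclusion.** The point holds in a limited form. As written, the number that determines the arm is assigned before baseline blood and the baseline interview, the envelope procedure is not reconciled with it, and masking is promised only after the intervention. Disclosure before the interview and a decodable ID are possibilities left open, not facts in the document.

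No size of bias can be established. The only firm statement is conditional: under analysis of covariance with correlation 0.7 and equal SDs, a spurious baseline difference of b SD shifts the effect by about 0.7b SD. The protocol's planned figures are unaffected. The point still matters before enrolment, because a baseline report given with knowledge of the arm, or one never collected, cannot be recovered in the analysis.

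**What to change.** Reorder Recruitment procedures as follows:

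1. eligibility and consent;
2. a study ID unrelated to arm;
3. baseline blood and interview;
4. the site supervisor opens the next sequential envelope for that site.

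Delete the clause by which the ID number determines the condition. Add one sentence stating that the number on forms and samples does not reveal the arm. As a minor clarification in the TAU description, state that the support-visit items are asked in all three arms, so that they cannot identify the arm to masked fieldworkers.

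The cost is a rewording of the procedure and, if the items are not already in the common questionnaire, a few more minutes of interview in two arms. Sample size, interventions and follow-up schedule stay as they are.

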#### Randomisation and blinding

Randomisation to one of the three conditions will occur at each of the four sites, i.e. the randomisation will be stratified by site. The randomisation code will be generated by computer generated tables. Treatment allocation will be done by site supervisors using pre-prepared consecutively numbered sealed, opaque envelopes, which will contain the group assignment. Fieldworkers will conduct the post-intervention outcome assessments masked to treatment allocation to ensure that the assessments remain unbiased and independent from the intervention sessions. Each counsellor will take part in only one intervention arm, and the wellness and alcohol reduction interventions will be run on different days of the week (based on alternating biweekly schedule) to minimise contact between participants who are randomly allocated to different arms, and to minimise contamination across the study arms. Given the study’s behavioural nature, the interventionists will not be blinded to which intervention the participants receive.

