### Phase two: randomised controlled trial

#### Design

The proposed parallel, individual RCT will use a repeated measures design (see Figure 1, Consort diagram). The study will be a three-arm comparison, with one pre-intervention observation and three repeated measures post-intervention observations per participant. Randomisation to interventions will be done within sites.

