Sample size estimates are based on the numbers of patients needed to detect differences between intervention and control groups in the mean number of drinks per day (past 30/60 days) at 3, 6, and 12 months post randomisation, our main outcome measure. A study among HIV patients found that the mean number of drinks per drinking days was 3.58 (Standard Deviation (SD): 1.81) under an enhanced MI vs. 4.75 (SD: 3.22) under the control arm [43]. For two-sided testing at a significance level of 5% and power of 90%, with one pre- and three post- intervention measures with a within subject correlation of 0.7 between measurements, the required sample size using analysis of covariance methods is 260. Of the 260 participants, 130 will be allocated to the alcohol intervention and 65 to each of the wellness and TAU arms. This imbalance of sample sizes for the treatment combinations can cause loss of power of statistical tests of differences between the group outcomes (e.g. means). It may also produce sensitive results in small samples when the assumptions of equal variance between groups are violated. Nonetheless, our choice of the imbalanced design was based on valid scientific and practical reasons, as the intervention combination we plan to assess is of great interest. Thus, the higher sample size in the main intervention arm (alcohol intervention) was chosen as it is statistically more efficient to have more subjects in this group as we will be comparing its effect to each of the other two interventions. This sample size also allows adequate power (>90%) to detect a modest effect size (0.25) for the within-subjects component, and for a potential interaction between- and within-subjects factors. However, the actual number of participants needs to be inflated to take into account attrition over time. We estimate an overall attrition rate of 20% and therefore need to recruit 325 participants to take into account this attrition. Assuming four sites, this would create a site-specific sample size of 82 (66 after attrition).

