We have no site-specific hypotheses, but if we want to include a safety margin for testing site specific effects of 0.30, we should allow for a site specific sample of 150 which would already include the attrition (120 per site before attrition). Of these, 75 would receive the alcohol intervention, and 38 each the wellness intervention and TAU. We will recruit participants from each site without an attempt to have equal numbers of men and women; we anticipate a ratio of about 2:1 females to males. Based on our prior data [44], we would estimate that about 40% of ART recipients will be alcohol drinkers. Of the alcohol drinkers, we estimate that about 15% would meet the criterion related to alcohol (have six (or four, if female) or more drinks on one occasion at least weekly, and score no more than 22 on the AUDIT). That research also suggests a participant eligibility rate of no more than 20%, so we would need to screen at least 750 patients at each site to reach our target sample of 150. Therefore we need to recruit participants from large facilities, suggesting that only hospital-based clinics would qualify as possible study sites. Thus, we plan to recruit participants from all four of the district hospitals in the Tshwane Health District, which cover a wide catchment area. The hospitals are: (1) Tshwane District Hospital, (2) Pretoria West Hospital, (3) Odi District Hospital, and (4) Jubilee Hospital. With four sites, our final sample size of 600 will include 300, 150 and 150 participants in the alcohol, wellness and TAU arms respectively. In the proposed district hospitals, there are HIV clinics in the form of separate outpatient departments (OPD). These HIV clinics carry very high volumes of patients, spanning the whole continuum of care.

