Given the repeated measures design, the main statistical analysis will involve repeated analysis of variance and analysis of covariance, using pre-treatment means and post-treatment means; or two-sample t-tests or chi-squared tests at the patient level data. The hypothesis that alcohol reduction will increase adherence will be tested via a repeated-measures Analysis of Variance (ANOVA). This will be an intent-to-treat (ITT) analysis. For our ITT analysis we will analyse our data based on the participants’ original allocation to the groups regardless of any subsequent group changes or participants’ degree of adherence to study protocols or their withdrawal from the study. We will assume data will be missing completely at random (MCAR) in order to enable imputation of missing data using standard techniques. We have postulated a main effect for the experimental condition without an interaction effect. In addition, we intend to use the CD4 T-cell counts and viral loads as objective biological endpoints, with the same statistical procedure being employed. Additional analyses will determine whether the pathway via reduction of alcohol consumption was indeed crucial to the differences in adherence. This can be measured by a cross-lagged panel design, where the alcohol in the time interval before the respective measurement of adherence will be assumed to have a significant effect. Structural equation modelling and path analysis will be used to test this assumption. Models will also be run with ART continuation as the endpoint. More advanced techniques, including generalised estimating equation and multilevel modelling, will also be employed. The association between the biomarker of alcohol consumption and self-reports of alcohol will be analysed using correlation and regression techniques with adjustments for possible confounders. The predictive ability of the biomarker will be assessed using sensitivity and specificity techniques to determine its ability to detect excessive self-reported consumption of alcohol.

#### Analyses for phase 3

Data analysis will be conducted using the same framework approach as described above for Phase 1. We will use the Phase 3 findings to assist with interpreting the findings of the RCT phase.

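### Randomisation is stratified by site, but the main analysis names no site term and allows t-tests or chi-squared tests that cannot include one (minor, conservative direction)

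*Protocol article*

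**What the plan says.** On design, the Design section states that "Randomisation to interventions will be done within sites", and Randomisation and blinding repeats that "the randomisation will be stratified by site". Study population and sample size considerations plans 150 participants per hospital, split 75 to the alcohol intervention and 38 to each of the other two arms. The method of allocation is computer-generated tables and numbered, sealed envelopes. No blocking or other balancing method is described.

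On analysis, the Phase 2 text says that "the main statistical analysis will involve repeated analysis of variance and analysis of covariance, using pre-treatment means and post-treatment means" and then continues "or two-sample t-tests or chi-squared tests at the patient level data". Later it adds: "More advanced techniques, including generalised estimating equation and multilevel modelling, will also be employed". No covariates, levels or clusters are given for any of these models, and site is not mentioned in the analysis section.

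Site appears otherwise only in the sample-size text. It states "We have no site-specific hypotheses", yet it raises recruitment from 325 to 600 to leave room for testing an effect of 0.30 within each site.

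**The concern.** When arms are balanced within hospitals, differences between hospitals cancel out of the treatment contrast. A test that ignores hospital still leaves those differences in its error term. Its standard error is then too large for the design, its p-values are too large and its intervals too wide. The stratification improves the estimate, but the test takes no credit for it.

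A plain two-sample t-test or Pearson chi-squared test cannot include site at all. Because the text lists these as acceptable forms of the main analysis, it leaves open whether the main test respects the randomisation. It also leaves open whether baseline is used, although the sample size was derived by ANCOVA with a pre-intervention measure. At stake are some precision and an unsettled choice between adjusted and unadjusted main tests. The validity of the estimates is not at stake.

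**Working it through.** **The plan's own figures.** The article gives no figure for the effect of site. Its attrition arithmetic reproduces: 260/0.8 = 325, 120/0.8 = 150, 4 × 150 = 600, and 600 × 0.8 = 480. The 260 itself does not reproduce from the stated inputs (difference 4.75 − 3.58 = 1.17; pooled SD √[(1.81² + 3.22²)/2] = 2.61; correlation 0.7; one pre and three post measures; 2:1:1 allocation). ANCOVA gives 100, and the closest variant, the post-treatment mean alone, gives 252. That is a separate matter, and nothing below depends on it.

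**Inputs.** From the article: four sites, two-sided 5% level, 90% power. Assumed, because the article does not give it: site explains a share v of residual outcome variance, shown for 2, 5 and 10%. Also assumed: exact balance of arms within site, suggested by the 75/38/38 plan but not guaranteed by any stated method.

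**Formulas.** With balance within site, the unadjusted standard error is too large by 1/√(1−v), so the effective critical value is c = 1.960/√(1−v).

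- True size = 2 × [1 − Φ(c)].
- If the site-adjusted test has 90% power, its non-centrality is 1.960 + 1.2816 = 3.2415, and unadjusted power = Φ(3.2415 − c).
- Share of sample lost, in power terms = 1 − [(3.2415 − c + 1.960)/3.2415]².

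| v | SE overstated | c | True size | Power | Sample lost (of 600) |
|---|---|---|---|---|---|
| 0 | 0% | 1.960 | 5.0% | 90.0% | 0 |
| 2% | 1.0% | 1.980 | 4.8% | 89.6% | 1.2% (7) |
| 5% | 2.6% | 2.011 | 4.4% | 89.1% | 3.1% (19) |
| 10% | 5.4% | 2.066 | 3.9% | 88.0% | 6.4% (39) |

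**Simulation check** (240 v 120 patients, four sites, 8,000 runs, exact balance within site). The t-test had size 0.045 at v = 5% and 0.040 at v = 10%, against about 0.050 with site in the model. Its power was 88.8% against 89.7% at v = 5%, and 86.7% against 88.8% at v = 10%. These gaps of about 1 and 2 points agree with the table.

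**Without balance within site.** The simulated size of the t-test was 0.050 at v = 5% and 0.046 at v = 10%. The simulation error is about √(0.05 × 0.95/8000) = 0.0024, so neither is clearly below 0.05. The conservatism depends on balance.

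**At the planned sample.** Take the stated 90% at 260 analysed at face value. At 480 analysed the non-centrality is 3.2415 × √(480/260) = 4.404. Power with site is Φ(4.404 − 1.960) = 99.3%. Without site, at v = 10%, it is Φ(4.404 − 2.066) = 99.0%.

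**Baseline.** At the article's correlation of 0.7, the variance of the mean of three post measures, relative to a single measure, is (1 + 2 × 0.7)/3 = 0.80. ANCOVA reduces this to 0.80 − 0.7² = 0.31. A t-test on change scores would give 0.80 + 1 − 1.4 = 0.40. A t-test on post-treatment values therefore gives up the gain on which the sample-size method relies.

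**The case against.** The strongest reply is that silence is not exclusion. ANCOVA is named in the main analysis and as the sample-size method. It and the repeated-measures models can carry site, as can the GEE and multilevel models. This is a condensed article, and a covariate list commonly sits in an analysis plan. That stands: a reader might infer that the main analysis leaves site out, but the text does not say so. What remains is the explicit listing of t-tests and chi-squared tests as alternative main analyses, which is a stated choice.

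A reader might also infer that balance within hospitals is secured by design. The per-site targets suggest that balance is intended, but no mechanism is stated. Without balance the test is not shown to be conservative.

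A reader might equate the site share with the share of participants lost, 0.02 × 600 = 12 to 0.10 × 600 = 60. With balance, that describes interval width. The loss in power corresponds to about 7 to 39.

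Finally, the fall from 90% to 88% is illustrative. The stated 90% belongs to 260 analysed, whereas about 480 are expected, where the gap is about 0.3 percentage points even at v = 10%. Adjusting for baseline drinking would also absorb stable differences between sites. All of this limits the size of the point, but it does not remove the mismatch.

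**Conclusion.** The point holds as a minor one. Randomisation is stratified by site, no site term is named in the main analysis, and two of the listed main tests could not contain one. If allocation is balanced within site and site explains 2 to 10% of residual variance, those tests run at a true size of about 4.8 to 3.9% and lose about 0.4 to 2.0 percentage points from a 90% power level. Both conditions are assumptions. The calculation is for a continuous outcome, and no figure is offered for binary outcomes tested by chi-squared. The documents do not support a reading that results would be biased or false positives inflated: the estimates are unbiased, and any error is on the cautious side.

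**What to change.** In the Phase 2 analysis text, state that the primary and secondary between-arm comparisons use ANCOVA or repeated-measures models (logistic or similar for binary outcomes), with site as a four-level fixed effect and the baseline value of the outcome as a covariate. This agrees with the ANCOVA basis of the sample size. Remove the two-sample t-tests and chi-squared tests as main analyses. If an analysis plan already specifies this, bring the article's wording into line with it. It would also help to state the balancing method used within site. Adding sex as a covariate is optional and not part of this point.

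The cost is one sentence of text and three degrees of freedom. No data collection or sample size changes.
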